**Fig. 4 Fig4:**
[figure not shown]
Randomization of study participants. SM = stress management condition; SM-B = Stress management + buddy condition; CC = control condition

Given the nature of the intervention, it is not possible to blind participants or the research team involved in delivering the intervention (IB and WV) and data collection (SS, AS and research assistants). Therefore, to reduce the risk of bias and to ensure that data collection is conducted in accordance with the ethical guidelines, research assistants will receive a training in data collection. Further, AS will maintain regular contact (biweekly meetings) with the research team to ensure that study procedures conducted are consistent with sound research design.

### Intervention and comparison groups

#### Intervention group with stress management course only (SM)

The SM program is an adaption of the existing course *Less Stress* developed by Trimbos institute [53] and has been tailored to meet the specific needs of low-SES participants. A core element of SM is its group-based format in which psycho-educative topics on stress responses and coping and motivation to stop smoking link up with cognitive and behavioral technique activities. The SM consists of four weekly sessions (1.5 h/session) and a follow-up session eight weeks later. The psycho-educative topics are discussed in the following order: introduction to stress, thinking habits, coping skills, setting boundaries, goal-setting and self-affirmation exercises, motivation to stop smoking and self-reflection. In session one, participants are offered general information on stress, the types of stress, stress signals and the effects of stress on health. After some theoretical background, participants learn the techniques of progressive relaxation and breathing exercises. Furthermore, BCT is utilized in the form of a 20- min goal-setting activity in which participants will be asked to set goals. This activity will be repeated once every month over the course of the study duration. In session two, BCT is utilized in the form of a 20-min self-affirmation activity carried out during the session. To increase self-affirmation, participants will be asked to write about their core values (i.e family, religion), why these values might be important to them and to rank these values in terms of their personal importance. The self-affirmation task is performed once over the course of the study period. Also, in session two, cognitive techniques (CT) are applied in which participants will be asked to identify, reframe and replace negative thinking habits with positive ones. In session three, participants will learn how to apply coping skills learned in previous sessions. In session four, participants will learn about healthier habits on how to reduce physical stress reaction and also rehearse the knowledge and techniques learned in previous sessions. Between sessions four and five, participants will be invited to a smoking cessation meeting during which professional smoking cessation counselors will provide information on strategies on how to stop smoking and maintain smoking abstinence. Participants will also receive self-help material and information on smoking cessation programs. Finally, in session five, participants will be asked to create their own Relapse Prevention Map (RPM). By creating a personalized RPM, participants will be able to plan ahead for high risk situations (i.e how to cope better with stress or how to resist smoking cravings).

#### Intervention group stress management with a buddy condition (SM-B)

The stress management with a buddy condition (SM-B) includes the same psycho-educative topics and exercises, CT and BCT activities as the SM condition. The SM-B utilizes one-to-one support through a buddy selected by the participant (the cursus trainer matches a buddy with a participant). A buddy, 18 year or older student or volunteer is recruited and subsequently trained by Indigo Rijnmond. The buddy receives a full training on the structure of the SM course program, his/her role on coaching and supporting a participant to get a grip of his/her personal finances (i.e trough organizing and managing finances). Upon completion of this training, a buddy pairs up with a participant and depending on the needs of the participants and if necessary, provides the following: 1) supports participant in managing and filling in tax/welfare papers; 2) helps a participant to get a grip over his/her finances (i.e by making a financial plan); 3) offers participant to overcome daily barriers (i.e arranging childcare); and 4) helps participant to set up a cost plan (i.e participant can track his/her spending on cigarettes). Over the duration of the course, the buddy meets up six times with a participant every second week in a public area. Depending on the needs and wishes of the participant, the buddy can meet up with a participant for one to two hours up to twelve times. After every appointment with the participant, the buddy reports back on the meetings with the participant, the topics discussed during the meetings and the help offered.

#### Control group

Participants in the CC are instructed to continue with their normal behavior. The CC group will complete the questionnaires and objective measurements at the equivalent times as the intervention groups, thus at T0, T1 and T2. After the control period, participants in the CC will be offered the intervention.

### Nudges

#### Head-start nudge

During the orientation sessions of the present study, eligible participants will receive a head-start nudge in the form of a stamp card. On a group-level, participants will be randomly assigned to either receive a half-filled stamp card (three out of eight boxes are already stamped) or an empty stamp-card. By already having a half-labelled stamp card, a participant will feel that he/she has already achieved ‘something’ and this thinking will further motivate the participant to complete the stamp card. Each time a participant attends a group session, he/she gets a stamp. In case a participant misses a session, he/she will receive a stamp only if he/she can provide a good reason (i.e no care available for a sick child). By not penalizing a participant for a missed session (given a good reason is provided), the participant will feel connected to the program and know that his/her presence was missed. This will motivate the participant to avoid missing any session in the future. A full stamp card means the participant will be rewarded with a full bag of groceries after completing the intervention.

#### Loss-aversion nudge

During the first group session, participants will be told that they will receive a ‘surprise’ prize (20€ voucher). The participants will be told that they can only claim the prize if they have attended all five group sessions, and if they have adhered to smoking abstinence. If participants have attended all five group sessions and their smoking abstinence is biochemically verified at T2, they will be awarded with this 20€ reward.

### Retention of participants

In order to maintain good participant retention, participants in the SM, SM-B and CC conditions will be rewarded with a gift voucher for their participation and completion of questionnaires at T0 (10€), T1 (10€), and T2 (5€). In Fig. 5, a schematic overview of the intervention and its components is given.

**Fig. 5 Fig5:**
[figure not shown]
Study timeline. SM = stress management condition; SM-B = stress management + buddy condition; CC = control condition; T0 = data collected at baseline; T1 = date collected 4 weeks after baseline; T2 = data collected 12 weeks after baseline

### Data collection methods

#### Outcome measures

The time schedule of study enrollment, interventions and assessments according to the SPIRT guidelines [54] can be found in Table 1.

**Table 1 Tab1:**
[figure not shown]
Timetable of study enrollment, interventions and assessments

*DASS-21* Depression, Anxiety and Stress Scales, *GATS* Global Adult tobacco Survey, *FTND* Fagerstrom test for Nicotine Dependence, *SM* Stress management, *SM-B* Stress management + buddy, *SF-12v2* Short Form Health Survey version 2, *PSWQ* Penn state worry questionnaire, *CSI-SF* Coping strategy inventory short form, *WVS* World Value Survey, *RSQ* Responses to stress questionnaire, *N/A* Not applicable

### Primary outcomes

#### Depression, anxiety and stress

The Depression, Anxiety and Stress Scales (DASS-21) is a validated self-report tool consisting of three 7-item measure assessing depression, anxiety and stress over the previous week using a 4-point Likert scale ranging from 0 to 3 (never, sometimes, often and almost always) [55]. Each subscale has a possible range of scores from 0 to 21 with higher scores indicating higher levels of depression, anxiety, and stress [55]. The total scores of each subscale is summed and multiplied by two to yield equivalent scores to the full DASS-42. The DASS-21 is a reliable screening tool for symptoms of depression, anxiety and stress, has been extensively utilized in a large non-clinical population [56] and has internal consistency and concurrent validity in acceptable to excellent ranges (α for depression, anxiety and stress: 0.94, 0.87 and 0.91, respectively) [57].

#### Smoking behavior and nicotine dependence

The Global Adult Tobacco Survey (GATS) questionnaire is used to record participant’s smoking status [58]. Participants will be asked to report the following: 1) current tobacco smoking status, 2) number of tobacco products smoked per day, 3) average tobacco products smoked per day, 4) frequency of consumption of different tobacco products, and 5) motivation to attempt quit. Additionally, participants will be asked to fill out the Dutch version of the Fagerstrom Test for Nicotine Dependence (FTND), which is a 6-item measure assessing smoking habit and dependence [59]. The items of the FTND are summed to yield a total score ranging from 0 to 10 with higher scores reflecting greater dependence. The Dutch FTND has demonstrated acceptable reliability (a = 0.66-0.71) [59] and correlates significantly with number of cigarettes smoked per day [60].

#### Financial health

To measure financial health, participants will be asked to report: 1) their total monthly income (< 1750€, 1750-2750€, > 2750€, don’t want to report); 2) whether they receive welfare (yes, no); 3) their spouse/partner’s total monthly income (don’t have any partner, < 1750€, 1750-2750€, > 2750€, don’t want to report, I don’t know); and 3) whether they have experienced money shortages in the past month (1 = never, 2 = sometimes, 3 = frequently, 4 = often and 5 = almost always). The proportion of participants in each category for each question asked will be calculated.

#### General health perceptions

The Short Form Health Survey version 2 (SF-12v2), is 12-item with three dimensions both for functioning (physical, social and role) and for wellbeing (mental health, general health perceptions and pain) [61]. In this study, participants will be asked to rate their general health on a Likert-type scale (1 = poor, 2 = fair, 3 = good, 4 = very good, and 5 = excellent). Low scores (poor) on the general health scale represent a person who believes his/her health to be poor and high score (excellent) represents someone who sees his/her health as excellent. The SF-12v2 has demonstrated relatively high reliability and validity estimates for the general population [61].

### Secondary outcomes (psychometric measures)

#### Worrying

The Penn State Worry questionnaire (PSWQ), a 3-item questionnaire is designed to measure worry (i.e. many situations make me worry). Participant responses on each item is rated on a 4-point Likert type scale (1 = never, 2 = sometimes, 3 = often and 4 = always). Subsequently item scores are summed up to yield a total score ranging from 0 to 15 with higher scores indicating greater tendency to worry [62]. The 3-item version of the PSWQ is chosen because it can be quickly administered, scored, have psychometric properties similar to the standard 16-item version [62] and has been reported to have an acceptable internal consistence reliability as evidenced by Cronbach’s α = 0.85 [62].

#### Coping strategies

The coping strategy inventory short form (CSI-SF), a 16-item self-report questionnaire derived from an original 78-item CSI [63], will be used to assess coping thoughts and behaviors in response to a specific stressor [64]. In the current study, participants will be asked to rate their coping strategies when confronted with a stressor on a 5-point Likert scale (1 = never, 2 = seldom, 3 = sometimes, 4 = always and 5 = almost always). Participants will receive scores for each first-tier subscale (engagement and disengagement) with scores ranging from 8 to 40. Further, for each of the four item subscales (problem-focused engagement, emotion-focused engagement, problem-focused disengagement and emotion-focused disengagement), participants will receive scores ranging from four (least adherent) to 20 (most adherent) [64]. Higher scores on the problem-focused engagement subscale indicates the participant is actively coping with a particular stressor, while higher scores on the emotion-focused disengagement subscale means the participant is coping negatively with a particular stressor. The CSI-SF is chosen because it contains 16-items, is quick and has been shown to be reliable for measuring coping strategies [64]. Good internal consistency of each coping scale assessed via Cronbach’s alpha (α = 0.58–0.72 [41] and (α = 0.56–0.80) have been demonstrated [65].

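### The CSI-SF response codes as printed do not rise with frequency (4 = always, 5 = almost always), although the stated score ranges need them to

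*Protocol article*

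**What the plan says.** Under Secondary outcomes, Coping strategies, the protocol article describes "The coping strategy inventory short form (CSI-SF), a 16-item self-report questionnaire" and states that participants in this study will answer on a 5-point scale whose upper codes are "3 = sometimes, 4 = always and 5 = almost always". The two lower codes are 1 for *never* and 2 for *seldom*.

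The scoring follows in the same section. There are two broad scales: "first-tier subscale (engagement and disengagement) with scores ranging from 8 to 40". For the four narrower subscales, "participants will receive scores ranging from four (least adherent) to 20 (most adherent". The direction is also stated: "Higher scores on the problem-focused engagement subscale indicates the participant is actively coping with a particular stressor".

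No other section restates the CSI-SF labels, corrects them or describes a recode.

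**The concern.** The subscale rule needs codes that increase with how often a strategy is used. The printed codes do so from *never* to *sometimes* and then reverse, because *always* gets 4 and *almost always* gets 5. Someone who uses a strategy all the time would score below someone who uses it nearly all the time, and could not reach the score described as most adherent.

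The article's other frequency scales do not do this. The money-shortage item under Financial health ends on its strongest label ("1 = never, 2 = sometimes, 3 = frequently, 4 = often and 5 = almost always"), and so does the worry scale ("1 = never, 2 = sometimes, 3 = often and 4 = always").

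Coping is the route by which the stress management course is meant to work. If the fielded form carries the printed labels and participants answer by the words, the coping scores would be noisier than they need be. If the form is sound and only the article is wrong, a later analyst could still interpret or score the data from the wrong labels.

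**Working it through.** **Inputs from the Coping strategies section:** 16 items; codes 1 to 5; two first-tier scales; four second-tier subscales.

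**Step 1. Reproduce the stated ranges.**
- First tier: 16 / 2 = 8 items, so 8 × 1 = 8 to 8 × 5 = 40. Stated: 8 to 40.
- Second tier: 16 / 4 = 4 items, so 4 × 1 = 4 to 4 × 5 = 20. Stated: 4 to 20.

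Both agree. The section does not use the word sum for this instrument, but the ranges are those of a plain sum of the 1-5 codes, and no recode of the top two codes is mentioned.

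**Step 2. Check the order.** By meaning, the labels run *never*, *seldom*, *sometimes*, *almost always*, *always*. Their printed codes in that order are 1, 2, 3, 5, 4, which is not increasing.

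**Step 3. Size in score points.**

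| Same answer to every item | 4-item subscale | 8-item scale |
|---|---|---|
| *Always* (code 4) | 4 × 4 = 16 | 8 × 4 = 32 |
| *Almost always* (code 5) | 4 × 5 = 20 | 8 × 5 = 40 |
| Difference | 4 | 8 |
| Share of the score span | 4 / 16 = 25% | 8 / 32 = 25% |

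These are maxima. Each single *always* answer costs one point against *almost always*.

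**Step 4. Effect on information, by assumption only.** The documents give neither item loadings nor the distribution of answers. The following are assumed: a one-factor ordinal model, four items, loadings of 0.5 to 0.7, answers split 10/20/30/25/15% across the categories in order of frequency, and 200,000 simulated respondents. Effective sample ratio = (correlation with the trait as scored / correlation with correctly ordered codes)².

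At loading 0.6, if everyone answers by the words, the correlation falls from 0.81 to 0.74, so the ratio is (0.74 / 0.81)² = 0.83. Alpha falls from 0.66 to 0.57. Over loadings 0.5, 0.6 and 0.7 the ratios are 0.82, 0.83 and 0.84, a loss of about 16-19% allowing for rounding.

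The result depends on how many people follow the words and how many follow position on a rising 1-5 row. At loading 0.6:

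| Share answering by the words | Ratio, codes as printed | Ratio, recoded by label |
|---|---|---|
| 0% | 1.00 | 0.83 |
| 25% | 0.95 | 0.87 |
| 50% | 0.91 | 0.91 |
| 100% | 0.83 | 1.00 |

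Under these assumptions, recoding by label helps only when more than half answered by the words. At half it gains nothing, and below half it makes the scores worse.

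**The case against.** The strongest reply is that this may be a slip in one parenthesis of an English article. Participants must have adequate Dutch, so the form they complete is presumably in Dutch, and the Pilot study section says the questionnaires needed refinement. If the form is in order, the collected scores are unaffected. That stands, and it limits the point to a discrepancy to be reconciled.

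Three stronger readings are tempting and are not supported.

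- A reader might infer that the coping subscales have lost reliability and that arm differences will shrink. The documents do not show the form, so this is conditional. The loss in the working rests on assumed loadings and an assumed answer split. Even the reduced alpha of 0.57 lies within the wider reliability range that the section cites (0.56 to 0.80). In the model, only about 1% of respondents choose the top category on all four items, so the 4-point maximum would be rare. The effective-sample measure also presumes a continuous score, whereas the Data analysis section names only logistic and multinomial regression for outcomes.
- A reader might infer that the scale lacks a step between *sometimes* and *always*. It does not: once the labels are ordered by meaning, *almost always* is that step.
- A reader might infer that the data should simply be recoded by label. The second table above shows that this can do harm.

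What the objection does not remove is that the labels and the scoring rule in the same section disagree as printed. This is an affirmative statement about this study's scale, not a detail left to a fuller document.

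**Conclusion.** The point holds in a limited form. The printed CSI-SF codes are out of order and conflict with the score direction stated beside them. Taken literally, they put uniform *always* answers 4 points below uniform *almost always* answers on a subscale with a 16-point span, and 8 points below on a scale with a 32-point span.

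Whether any data are affected depends on the fielded form. If they are, the loss of effective sample size lies between 0% (nobody answers by the words) and about 16-19% (everybody does), under the assumptions in the working. The effect is confined to a secondary outcome and to the top two response categories. The primary outcomes and the sample size are not touched. This is a minor correction that is worth making while the trial is still running.

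**What to change.** 1. Compare the labels and codes in the article with the Dutch form given to participants.
2. If the form's options rise in order, correct the labels or codes in the text, so that the data are scored and interpreted by the real labels.
3. If the form carries the printed order, do not recode automatically. Keep the same form for each participant at T0, T1 and T2, because changing labels between visits would weaken within-person comparison. Report the coping subscales under both codings, or with the top two categories merged, as a sensitivity analysis. Merging gives the same score whichever way people answered, at the price of some detail at the top of the scale.

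The cost is one check of the form, followed by either a text correction or a few lines of code and one additional table. No new data are needed.

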#### Social support

Social support will be measured based on a single item by asking participants to list the number of people in response to the question ‘how many people can you turn to for support when experiencing stress?’

#### Self-control

Using the World Values Survey questionnaire (WVS) [66], self-control will be measured using an item where participants will be asked how much freedom of choice and control they have over their lives (1 = no control, 10 = full control). Lower levels mean individuals have no control over their lives, whereas higher levels mean individuals have full control over their lives.

#### Coping and involuntary responses to financial worries

The Responses to Stress Questionnaire (RSQ) is designed to capture the way individuals cope with and react and adapt to stressors [67]. In the current study, the stressor is financial worries (money troubles). Using a single-item, participants will be asked to rate having control over their finances on a 10-point Likert-type scale (1 = no control, 10 = full control). Lower values represent no control and higher values represent full control. The RSQ has been previously tested for different stressors experienced by different populations (children and adults) and have demonstrated strong reliability and validity [67, 68].

### Objective measures

#### Carbon monoxide breath test

Carbon monoxide (CO) measured in parts per million (ppm) and carboxyhemoglobin (COHb) measured as percentage of oxygen replaced) are indicators of smoking status. CO_breath_ and COHb levels will be measured using the Micro+ Smokerlyzer® (Bedfont Scientific Ltd.) by a trained research staff at T0, T1, and T2. Briefly, participants will be asked to hold their breath for 15 s and subsequently to exhale slowly and fully into the mouthpiece of the instrument during which CO_breath_ is recorded. If a participant is not able to hold his/her breath for 15 s, he/she is allowed to hold his/her breath as long as possible and subsequently exhale in the SmokerLyzer. CO_breath_ levels are defined as equivalent to nonsmoker (0-6 ppm), borderline smoker (7-9), light smoker (10-15 ppm), moderate smoker (16-25 ppm), heavy smoker (26-35 ppm) and very heavy smoker (36+) [69]. In this study, a cut-off value of 10 ppm will be used to discriminate smokers from nonsmokers. This value is programmed into the SmokeLyzer device [69] and equals that recommended by other studies [70, 71]. Prior to use, the device is calibrated according to the manufacturer’s instructions and will be re-calibrated again during data collection as an additional measure to ensure accuracy of results. The Micro+ Smokerlyzer® is non-invasive, easy to use, has a precision of < 2% [69] and has been validated in other populations including low-SES [72].

